### 2.4. Intervention Masking

Participants are informed that two different group programmes are compared, but no detail is given about the difference between them. Most outcomes are not expected to be affected by the investigators’ knowledge of the treatment arm. An assessment of functional capacity is performed, whenever possible, by explorers unaware of the participant’s assigned treatment.

### 2.5. Standard Treatment

The standard treatment (control group) consists of a structured, educational, and behavioural programme of eight 2-h, fortnightly sessions, followed by 1-h monthly sessions until surgery. Table 1 describes the contents of the sessions.

At the first session, all participants are given the contents of the education programme in writing and are asked (and trained) to start recording their physical activity by means of a free, mobile app (*Google Fit*) downloaded in their smartphones or an activity tracker, if they owned one, for motivation and monitoring of adherence. To avoid contamination between treatment arms, the control and intervention groups are scheduled every other week.

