## Abstract

Bariatric surgery is the most efficacious treatment for obesity, though it is not free from complications. Preoperative conditioning has proved beneficial in various clinical contexts, but the evidence is scarce on the role of prehabilitation in bariatric surgery. We describe the protocol and pilot study of a randomized (ratio 1:1), parallel, controlled trial assessing the effect of a physical conditioning and respiratory muscle training programme, added to a standard 8-week group intervention based on therapeutical education and cognitive-behavioural therapy, in patients awaiting bariatric surgery. The primary outcome is preoperative weight-loss. Secondary outcomes include associated comorbidity, eating behaviour, physical activity, quality of life, and short-term postoperative complications. A pilot sample of 15 participants has been randomized to the intervention or control groups and their baseline features and results are described. Only 5 patients completed the group programme and returned for assessment. Measures to improve adherence will be implemented and once the COVID-19 pandemic allows, the clinical trial will start. This is the first randomized, clinical trial assessing the effect of physical and respiratory prehabilitation, added to standard group education and cognitive-behavioural intervention in obese patients on the waiting list for bariatric surgery. Clinical Trial Registration: NCT0404636.

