### 2.6. Intervention (Prehabilitation)

The intervention group receives the same programme as above, but each 2-h standard session is followed by half an hour specific training, aimed at increasing physical activity, functional capacity, and respiratory muscle strength.

At the end of the first session, the participants in the intervention group are given a device for incentive spirometry (Figure 2), an inspiratory valve (Figure 3), and elastic non-latex resistance bands (*TheraBand^®^*, Akron, OH, USA), which are colour-coded according to their resistance (yellow, blue, black). Patients are trained in the use of the devices.

Participants are also given general recommendations on physical activity, such as avoiding high UV exposure, using adequate clothing, and shoes and avoiding exercise when sick. They are advised to walk for at least 30 min daily, and then gradually increase this, according to tolerance. The first and final 5-min periods are used for warm-up and cool down, respectively. Participants are also advised to practice all exercises daily and to record them and bring the registers to the following session.

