### 2.7. Outcomes

The primary outcome is the change in body weight between the start of the programme and the time of surgery.

Secondary outcomes include: changes in body composition, comorbidities, changes in eating behaviours, health-related quality of life, functional capacity, length of hospital stay after surgery and short-term complications of surgery.

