### 2.12. Adherence to the Intervention and Physical Activity

Adherence to the intervention is assessed by the attendance at the sessions. Physical activity is monitored using an activity app (*Google Fit* or the manager of an activity tracker) downloaded on a smartphone, as well as the Spanish short version of the International Physical Activity Questionnaire [62].

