## 3. Results

Participants in the pilot study had their first visit between 8 August 2019 and 13 September 2019, and the interventions took place between October 2019 and January 2020. 

Out of the 51 patients on the waiting list, expected to be operated on at least 4 months after recruitment, 19 accepted to participate. The main reasons given for declining were participation in preoperative groups in another centre (on a different island), distance to the training site and schedule problems, mainly due to working hours. None of the patients refused to participate or was excluded due to linguistic barriers. A total of 15 (14 women) attended the first visit and were randomized. Their mean age was 40.0 ± 10.0 years, baseline BMI, 46.7 ± 5.9 kg/m^2^, and waist circumference 134.2 ± 12.0 cm. The most frequent complications of obesity were OSA (54%), osteoarticular disorders (40%), asthma (33.3%), hypertension (33.3%), infertility (35.7%), chronic venous insufficiency (28.6%), diabetes (26.7%), and dyslipidaemia (26.7%). Seven patients were randomized to the intervention group and 8 to the control group. Their baseline features are displayed in Table 2.

The first eight sessions took place between October 2019 and January 2020. Three participants dropped out before even starting the intervention (one travelled abroad, another one said the timing of the sessions was inconvenient, and the third did not give a specific reason). The rest attended between one and six sessions. Only five participants completed follow-up, three in the intervention and two in the control group. Of the ten patients not completing the programme, seven interrupted it due to early surgery. Unlike what was initially planned, because of the low attendance at the sessions, we decided to merge both treatment groups from session 2, since group intervention was not possible otherwise. The control group left after the standard session finished, whereas the intervention group joined the physiotherapist team thereafter.

The five participants completing the follow-up lost an average of 0.54 ± 5.2 kg (Intervention group +1.6 ± 4.3 kg; Control group −3.8 ± 5.7 kg) and the final BMI was 48.1 ± 7.6 kg/m^2^ (Intervention Group 45 ± 7.3 kg/m^2^; Control group 52.69 ± 10.6 kg/m^2^). Given the small sample size, no statistical analysis was performed and no conclusions can be drawn.

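### App or tracker recording of physical activity starts only at session 1, so the objective measure of this secondary outcome has no pre-programme value

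*Protocol article*

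**What the plan says.** All places are in the protocol article.

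- **Abstract.** Physical activity is an outcome: "Secondary outcomes include associated comorbidity, eating behaviour, physical activity, quality of life, and short-term postoperative complications".
- **Section 2.7 (Outcomes).** The secondary list does not contain it. It runs: "changes in body composition, comorbidities, changes in eating behaviours, health-related quality of life, functional capacity, length of hospital stay after surgery", followed by short-term surgical complications.
- **Section 2.12.** "Physical activity is monitored using an activity app" or the software of a tracker, "as well as the Spanish short version of the International Physical Activity Questionnaire". Adherence is assessed separately, by attendance.
- **Section 2.5.** At the first session, participants in both arms are "asked (and trained) to start recording their physical activity by means of a free, mobile app", or a tracker if they own one. The stated purpose is "for motivation and monitoring of adherence".
- **Section 2.6.** In the intervention arm each standard session is followed by half an hour of specific training. Of these participants it says: "They are advised to walk for at least 30 min daily".
- **Table 1.** Session 1, given to both arms, covers healthy lifestyle, weight loss, physical activity and how to monitor it.
- **Table 2.** Baseline activity is reported only as IPAQ category.

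**The concern.** The added training is meant, among other things, to raise physical activity (section 2.6). Recorded activity is therefore a natural check on whether the intervention does what it sets out to do. Of the two instruments in 2.12, only the app or tracker is objective; the IPAQ is self-report. The six-minute walk and handgrip tests measure functional capacity, which is a different thing.

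If recording starts on the day the programme starts, no objective reading describes the participant beforehand. No later analysis can recover a reading that was never taken, so the matter cannot be left to an analysis plan. At stake are the change from baseline in recorded activity and the ability to remove stable differences between persons, and between a phone app and a worn tracker, from the comparison.

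**Working it through.** The article states no figure on this point, so there is none to reproduce. The check is mainly one of timing.

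**1. Order of events**

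| Step | Source | App or tracker recording? |
|---|---|---|
| Consent, envelope opened | 2.3 | No |
| Baseline assessment tests | 2.3, 2.9, 2.11 | No |
| Session 1: activity education in both arms; added training in the intervention arm | 2.5, 2.6, Table 1 | Starts here |
| Sessions 2 to 8, then monthly until surgery | 2.5 | Continues |

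No section provides a run-in. A participant who already owned a tracker might hold earlier data, but no section provides for collecting it.

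**2. Is there room for a run-in?** Pilot first visits ran from 8 August to 13 September 2019, and sessions began in October (section 3). The shortest possible gap is 13 September to 1 October, 18 days or 2.6 weeks. The longest, if the first session fell at the end of October, is 8 August to 31 October, 84 days or 12.0 weeks. These gaps run from the first visit; the article does not date the baseline tests separately. Seven days fit if those tests are held at least a week before session 1.

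**3. What a baseline covariate would gain.** With correlation r between a person's baseline and follow-up reading, adjustment leaves a fraction 1 − r² of the residual variance, and the standard error is multiplied by √(1 − r²). The article gives no r, so 0.5 to 0.7 is an assumed range.

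- r = 0.5: 1 − 0.25 = 0.75, so 25% less variance; √0.75 = 0.87, standard error 13% lower.
- r = 0.7: 1 − 0.49 = 0.51, so 49% less variance; √0.51 = 0.71, standard error 29% lower.

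This applies only to participants with both readings.

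**4. Who would have no reading at all?** Section 3 reports: "Three participants dropped out before even starting the intervention". That is 3/15 = 20% (exact 95% interval 4% to 48%). If the same share held among the planned 80, about 80 × 0.20 = 16 would have no app record. The carry-forward rule in 2.15 would have nothing to carry for them.

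**5. The other instrument.** In Table 2 the baseline IPAQ is unavailable for 2 participants in each arm: 4/15 = 27%. A self-reported baseline exists, but it was incomplete in the pilot.

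**The case against.** The strongest reply is that the app is not an outcome instrument. Section 2.5 places it within standard treatment and gives motivation and adherence as its purpose, and 2.7 does not list physical activity. This carries weight: outcome status rests on the abstract alone. It does not dispose of the point. Section 2.12 assesses adherence by attendance and separately names the app as the means of monitoring activity. If adherence is the only intended use, the article should say so and name the IPAQ as the activity outcome.

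A second reply is that randomised arms can be compared on activity during the programme without any baseline. That is correct. Section 2.15 plans between-group tests, and such a comparison is unbiased without a starting value.

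Three stronger readings are tempting, and the article does not support them.

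- A reader might infer that the first recorded day is treated in one arm and untreated in the other. Table 1 shows that both arms receive lifestyle and activity education at session 1; only the added component differs.
- A reader might infer that the treatment effect will be partly subtracted because the first recorded week will serve as baseline. No section proposes that analysis. It is something to rule out in the text, not an error already made.
- A reader might infer that earlier recording would cure the gap from participants who never start. It would give them a baseline but no follow-up value, and carrying that baseline forward would merely record them as unchanged.

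**Conclusion.** The point holds as a modest improvement to a secondary outcome. The article starts its only objective activity measure once the programme is under way in both arms, so no pre-programme value exists. Change in recorded activity cannot be computed, and person or device differences cannot be adjusted for. Validity of the between-arm comparison is not in question, and the primary outcome, weight change, is unaffected.

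The size is a precision gain of 25% to 49% less residual variance at an assumed r of 0.5 to 0.7, among those with both readings. A reader might convert this into a larger effective sample for the whole trial. That is not warranted: the correlation is unsourced, the conversion needs complete app data on all 80, and the unadjusted tests named in 2.15 would not deliver the gain without a covariate-adjusted comparison.

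**What to change.** 1. Amend 2.5 and 2.12 so that the app or tracker is set up at the existing baseline visit in both arms and records at least 7 days before session 1.
2. Have each participant keep the same device type throughout.
3. Compare follow-up activity between arms with the pre-programme reading as covariate, and state that no reading from session 1 onward serves as baseline.
4. Reconcile the abstract with 2.7 on whether physical activity is an outcome. If the app is meant for adherence only, say so and name the IPAQ as the activity outcome.

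Under 2.3 the baseline tests follow the opening of the envelope, so the reading would come after randomisation but before the programme. Since 2.4 withholds from participants how the programmes differ, this is a minor limitation.

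The cost is protocol wording and a few minutes at a visit that already takes place. The trial has not started, and the Discussion says protocol changes are to go to the Ethics Committee anyway. The downside is that self-recording before the programme may raise activity slightly, in both arms alike. The change does not supply follow-up data for participants who never start.

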### 2.6. Intervention (Prehabilitation)

The intervention group receives the same programme as above, but each 2-h standard session is followed by half an hour specific training, aimed at increasing physical activity, functional capacity, and respiratory muscle strength.

At the end of the first session, the participants in the intervention group are given a device for incentive spirometry (Figure 2), an inspiratory valve (Figure 3), and elastic non-latex resistance bands (*TheraBand^®^*, Akron, OH, USA), which are colour-coded according to their resistance (yellow, blue, black). Patients are trained in the use of the devices.

Participants are also given general recommendations on physical activity, such as avoiding high UV exposure, using adequate clothing, and shoes and avoiding exercise when sick. They are advised to walk for at least 30 min daily, and then gradually increase this, according to tolerance. The first and final 5-min periods are used for warm-up and cool down, respectively. Participants are also advised to practice all exercises daily and to record them and bring the registers to the following session.

#### 2.6.1. Physical Conditioning

It consists of four resistance exercises with elastic bands, that are to be performed twice daily, for 15–20 min per time, until the following scheduled session. Participants receive spoken and written instruction, as well as practical demonstrations. Four exercises involving large muscle groups of both the upper and lower extremities are proposed (e.g., Kabat’s diagonal, frontal elevation and aperture of the arms, shoulder elevation and rolling, and squats combined with elbow flexion). The concentric phase of muscle contraction is performed during expiration. Each exercise is repeated 15 times per series, and 2–3 series are planned, with recovery time in between. Low resistance bands are used at the beginning of the programme and are progressively changed to higher resistance bands.

#### 2.6.2. Minimal Preoperative Respiratory Physiotherapy Intervention

Incentive spirometry: The purpose of incentive spirometry is to facilitate a sustained, maximal inspiration (SMI). An SMI is a slow, deep inspiration from the Functional Residual Capacity up to the total lung capacity, followed by 4–8 s breath-hold, mimicking natural sighing. We use *Coach 2*^®^ (*Portex*^®^, Smith-Medicals, Minneapolis, MN, USA) 500–4000 mL devices which provide visual cues to the patients that the desired flow or volume has been achieved (Figure 2). This serves as a motivation and a goal for the patient to try to meet, by repeating the maximal effort frequently. We recommend four repetitions of this maneuver both standing and sitting. Patients are encouraged to use the device twice daily.Respiratory exercises: Participants are taught how to perform specific respiratory exercises (breathing with pursed lips, quick and slow expiratory techniques, in order to manage secretions, and assisted cough with the protection of the surgical wound).Inspiratory muscle training: This is performed using an inspiratory valve (0–70 cm H_2_O) (*Orygen Inspiratory Valve*, Forumed S.L., Gerona, Spain) (see Figure 3) [46]. Training starts at 30% of the maximal inspiratory pressure (MIP) with progressive 10 cm H_2_O increments from session to session, according to the participant’s tolerance to the exercises. Patients are advised to repeat these exercises for 10 min twice daily, at 2 min intervals.

### 2.7. Outcomes

The primary outcome is the change in body weight between the start of the programme and the time of surgery.

Secondary outcomes include: changes in body composition, comorbidities, changes in eating behaviours, health-related quality of life, functional capacity, length of hospital stay after surgery and short-term complications of surgery.

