### 2.9. Body Composition

Body composition is assessed at the baseline visit. Weight is assessed with a calibrated bioimpedance (*Tanita BC 420 MA III*, Tokyo, Japan) to the nearest 0.1 kg, and height, using a stadiometer to the nearest 0.5 cm, without shoes and with light clothing. Body Mass Index (BMI) is then calculated as weight (in kg) divided by height (in meters)^2^. Body composition is analyzed through Vectorial Bioimpedance by tetrapolar impedance plethysmography using an electric alternating current flux of 400 µA at an operating single sinusoidal frequency of 50 kHz (*Nutrilab™*, Akern, Firenze, Italy in resting conditions. Standard whole-body measurements are performed according to the manufacturer’s guidelines on the right side of the body with the subjects in supine position with their arms and legs abducted, and the skin cleaned to ensure good contact. The thighs are checked not to be in contact with each other and the arms not to be touching the sides of the body. Electrodes are placed on a line between the radial and ulnar styloid processes on the dorsum of the wrist and on a line between the medial and lateral malleoli on the dorsum of the ipsilateral foot, overlying the head of the third metacarpal on the dorsum of the hand and the third metatarsal on the dorsum of the foot. Total body water, fat-free mass, fat-free mass percentage, fat mass, fat mass percentage and body cell mass are determined according to the formulas of Kotler et al. [48], and bioelectrical parameters of resistance, reactance, and phase angle are registered.

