### 2.14. Surgery

Information about the date, surgical procedure (including Foucher, staple size and type, gastric pouch size, gastrojejunal anastomosis diameter, common channel length), length of hospital stay, and early (first 30 days) complications are obtained from the participant’s clinical record. Post-operative complications are classified according to the Clavien–Dindo classification [63].

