The pilot study has indeed led us to reflect on the possible causes of low acceptance of and adherence to the programme, as well as establishing mechanisms to overcome this. Seventy percent of the participants were operated on before the group intervention was completed. Therefore, coordination between the medical and surgical teams is needed, to improve the timing of the treatment. Indeed, patients who are further down on the waiting list will be invited to participate, in coordination with the Surgery Department. Moreover, additional measures are planned to improve motivation and acceptance of and adherence to the programme. More information about the group intervention will be given to patients when they are referred to our centre for bariatric surgery. An informative leaflet is being designed by the Endocrinology and Surgery Departments and will be explained and given to the patients in their first visit to them. The inclusion of this kind of approach in the routine care of patients with obesity should increase its acceptability. Alternative scheduling, or a combination of physical and online sessions, might also improve adherence in the case these measures are insufficient. These changes to the protocol will be submitted to the Ethics Committee.

The main strength of our study is the multidisciplinary approach of the intervention, which includes not only nutritional, behavioural, and psychological interventions, but also physical conditioning and respiratory training. The fact that it is designed as a randomized, controlled trial sets high expectations regarding the quality of the results. Once the SARS-CoV-2 allows, the clinical trial will start.

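### The primary outcome runs to surgery, but patients operated on early are counted as lost, and the article names no weighing at surgery

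*Protocol article*

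**What the plan says.** All references are to the protocol article.

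- **Endpoint (2.7):** "The primary outcome is the change in body weight between the start of the programme and the time of surgery". Section 2.5 fits this: after the eight fortnightly sessions, monthly sessions go on up to the operation, so session 8 is not the endpoint.
- **Weighing (2.9):** "Body composition is assessed at the baseline visit". The section describes how weight is taken and names no other occasion.
- **Data at surgery (2.14):** the list covers the date and detailed features of the procedure, and then "length of hospital stay, and early (first 30 days) complications are obtained from the participant’s clinical record". Weight is not on it.
- **Analysis (2.15):** intention to treat, with missing values filled by LOCF. The sample size of 80 assumes no loss to follow-up.
- **Pilot (Results and Abstract):** the number randomised is given as follows: "A total of 15 (14 women) attended the first visit and were randomized". Most of the remaining patients left through surgery: "Of the ten patients not completing the programme, seven interrupted it due to early surgery". The Abstract ties completion to a return visit: "Only 5 patients completed the group programme and returned for assessment". The Results split these five completers as three in the intervention arm and two in control.
- **Discussion:** it attributes most of the follow-up losses to the operation, and adds: "Seventy percent of the participants were operated on before the group intervention was completed".

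**The concern.** If the endpoint is weight at surgery, early surgery brings the endpoint forward; it does not make it missing. The pilot handled it the other way round. Leaving the programme through surgery was a loss, and weight change was summarised for those who finished the sessions and returned. Even those five weights are not said to be weights at surgery.

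Two things are at stake if this practice carries into the main trial. First, finishing the programme depends on time to surgery and attendance, both of which arise after randomisation, so a summary of completers is not protected by the randomisation. Second, the LOCF rule in 2.15 would act on patients whose endpoint could have been measured. If baseline is their only earlier weight, each would be given a change of exactly zero.

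**Working it through.** **1. The reported change belongs to the completers.** The Results give +1.6 kg for the intervention group (3 completers) and −3.8 kg for control (2 completers). Weighted mean: (3 × 1.6 + 2 × (−3.8)) / 5 = −2.8 / 5 = −0.56 kg. The article reports an average loss of 0.54 kg, which agrees within rounding. No early-surgery patient contributes.

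**2. The article's 70%.** Inputs from the Results: 15 randomised, 5 completers, 10 non-completers, 7 of these with early surgery.
- Of non-completers: 7/10 = 70%.
- Of participants: 7/15 = 46.7%.

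The Discussion's figure reproduces only with non-completers as denominator, although it names participants. Its other statement, that most losses were due to surgery, is correct (7 of 10).

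**3. Share with a primary outcome in the pilot.**
- Early surgery counted as loss: 5/15 = 33%.
- Early surgery counted as reaching the endpoint: (5 + 7)/15 = 12/15 = 80%.
- Remainder: 3/15 = 20%, the patients who left before starting.

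This takes the three and the seven as separate people. The counts fit (3 + 7 = 10), but the article does not say so.

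**4. What LOCF would do.** Let p be the share operated on early, taken as equal in both arms, and let Δe and Δc be the true group differences in early-operated and other patients.
- With weights at surgery, the overall difference is (1 − p)Δc + pΔe.
- With baseline carried forward for the early-operated, it is (1 − p)Δc + 0.
- The shortfall is pΔe.

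If the programme works in the same direction in both subsets, this moves the estimate toward zero. With unequal shares, the direction is not fixed. The pilot does not settle this: there were 7 − 3 = 4 non-completers in the intervention arm and 8 − 2 = 6 in control, so the seven could divide anywhere from 1 and 6 to 4 and 3.

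**5. Illustration at 80 patients.** The plan's own figures come first. Detectable difference = (1.96 + z) × SD × √(2/n), with n = 40 per arm and SD 11 kg:
- 80% power: (1.96 + 0.842) × 11 × √(2/40) = 6.89 kg.
- 90% power: (1.96 + 1.282) × 11 × √(2/40) = 7.97 kg.

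These are the 7 and 8 kg of 2.15, although the article pairs them with the two power levels in reverse order, which is a separate matter. Now apply the pilot shares and analyse observed weights only:

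| Early surgery treated as | Observed of 80 | n per arm | Power for 8 kg, SD 11 |
|---|---|---|---|
| loss | 80 × 5/15 = 26.7 | 13.3 | Φ(8/4.26 − 1.96) = 47% |
| endpoint reached | 80 × 12/15 = 64 | 32 | Φ(8/2.75 − 1.96) = 83% |

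Here 4.26 = 11 × √(2/13.3) and 2.75 = 11 × √(2/32).

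**The case against.** The strongest reply is that much of this is silence in a condensed article. Figure 1 and the full protocol are not shown, and a visit schedule is commonly left to them. Section 2.9 is mainly about technique and cannot mean baseline only: 2.7 lists change in body composition as an outcome, and the Results give follow-up weights. This stands. A reader might infer that no weight is taken at surgery, but the text supports only that the article names none.

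A reader might also infer that the seven have endpoint values that were discarded. They reached the time point; whether anyone weighed them then is not stated. Nor does the article say that the main trial will be analysed in completers. Section 2.15 specifies intention to treat, and the Results decline to draw any conclusion from the pilot. Differential loss by arm is likewise unproven, because the arm split of the seven is not given.

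The scaling to 80 patients is no forecast. It carries the rates of a 15-patient pilot forward unchanged, while the Discussion plans to invite patients with a longer expected wait, in coordination with the surgeons.

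What the reply does not remove is the conflict between an endpoint set at surgery and the labelling of operated patients as lost. The planned measures may make early surgery rarer, but they do not say how such a patient is classified or weighed.

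**Conclusion.** The point holds as an inconsistency within the article: the endpoint is defined by surgery, while follow-up in the pilot was defined by the programme. Its size in the pilot is 33% against up to 80% of randomised patients with a possible primary outcome, given that the three and the seven do not overlap and that a pre-operative weight could have been taken. The consequences for the main trial are conditional. They arise if early-operated patients are again treated as missing, and the zero-change form of LOCF further requires that baseline is their only earlier weight. The 27 against 64 patients and the power figures are illustrative only. The denominator error in the Discussion is certain but minor. Since this decides whether the primary outcome is observed, it should be settled before the main trial starts.

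**What to change.** - In 2.7, 2.9 and 2.14, define the primary value as the last pre-operative weight, taken at surgical admission or the last pre-operative visit by the same weighing method as at baseline.
- Collect it for every randomised patient who is operated on, regardless of attendance.
- State that surgery before session 8 is not loss to follow-up, so that LOCF applies only where no such weight exists.
- In the Discussion, change the 70% to refer to non-completers (7/10), or give 47% of participants (7/15).

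Repeating body composition at admission and cross-calibrating scales are optional. A coherent alternative is to move the endpoint to the end of the programme and say how earlier surgery is handled, but that changes the question that 2.7 asks.

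The cost is protocol wording and one weighing at a contact that takes place anyway, with no extra patients. Protocol changes are already due to go to the Ethics Committee, so this can go with them.
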